#### Cognitive Restructuring (Session 2)

In the first step, participants identify negative cognitions and distorted beliefs about sexual intercourse, genital pain, and sexuality in general, and learn how cognitions can influence emotions and behavior. In the second step, they restructure and replace these cognitions with more helpful and encouraging ones. These cognitions are also rehearsed as coping self-statements during the exercises.

#### Non-Judgmental Awareness (Session 2)

By learning about and practicing non-judgmental awareness, participants might be able to interrupt automatic processes of negative cognitions. They are instructed to observe their cognitions and emotions in response to sexual situations without interpreting, judging, reacting to or suppressing them. To get used to the principles of non-judgmental awareness, participants are asked to practice it not only in sexual but also in nonsexual day-to-day situations.

#### Muscle and Breathing Relaxation (Session 3)

Participants will learn PMR in combination with breathing relaxation (69). By learning to flex and relax muscles voluntarily, participants can begin to control their body tension. Guided by an audio file, they start to practice PMR and eventually switch to a shorter version that can also be integrated into day-to-day activities. Based on the principles of PMR, pelvic floor exercises are then introduced in a video tutorial. These exercises are meant to increase proprioception and decrease hypertonicity of the pelvic floor.

#### Attention-Focusing for Pain Management (Session 3)

In Session 3, participants are also introduced to the relationship between vaginal pain and anxiety, and the consequences of pain and fear of pain on sexual arousal and muscle tension. They are asked to explore exacerbating and alleviating factors that influence their genito-pelvic pain. During attention-focusing, patients localize the pain center, describe the pain as images, and use suggestive pain transformation to alter the pain.

#### Body Exposure and Genital Self-Exploration (Session 4)

The internal and external female genitals and the anatomy of pelvic floor are introduced and illustrated with drawing. This treatment component also addresses the physiological processes during arousal and sexual intercourse. Participants are introduced to a body exposure exercise and asked to explore their vagina in front of a mirror. The approach taken here is non-judgmental and mindful of negative cognitions and emotions. Genital self-exploration is complemented by other, shorter body exposure exercises that are meant to enhance participants’ positive self-perception of their bodies and desirability.

#### Sensate Focus (Session 4)

The aim of the sensate focus exercises is to promote physical intimacy and reduce associated stress, pressure, and anxiety by emphasizing the experience of sensual pleasure by the couple over intercourse or orgasm (70, 71). Sensate focus exercises foster sensual body awareness and allow participants to become better acquainted with their own and their partners’ bodies and erogenous zones. These exercises involve progressive steps in which partners touch and give massages to each other (1) first nongenitally, wearing clothes and then only underwear, (2) with genital touching but not aiming for sexual arousal, and (3) genital touching that can lead to sexual arousal. During the exercises, the participants and their partners switch active and passive roles and are asked to communicate their feelings and experiences to learn more about their own and their partner’s sensual and sexual pleasures.

#### Building Sexual Desire and Arousal (Session 6)

One of the goals of the treatment is to increase sexual desire and arousal, as both influence vaginal penetration and pain. Information on self-stimulation and masturbation, e.g., techniques, is provided.

#### Gradual Vaginal Exposure (Sessions 3, 5–7)

Gradual vaginal exposure is combined with PMR and pelvic floor exercises. The exercises involve (1) insertion of one and two fingers by the woman and (2) one and two fingers by the partner, whereby the woman guides the partner’s hand while inserting his finger or fingers, (3) self-insertion of dilators of increasing sizes, with the largest dilator being similar in size to a penis, and (4) insertion of dilators of increasing sizes by the partner guided by the woman. Additionally, participants are encouraged to keep the dilator inside the vagina for a longer period of time (up to an hour) to get used to the feeling and to increase the habituation effect. Participants are advised to choose a larger dilator if they are comfortable with repeated insertions. These gradual exposure exercises are accompanied by detailed step-by-step instructions and also include, for example, suggestions for preparing for the exercises, sitting postures and recommendations that will help women deal with possible difficulties.

#### Sexual Intercourse (Session 7)

Step-by-step insertion exercises with the penis include (1) touching the vagina with the erect penis without insertion, (2) inserting the erect penis without moving, and (3) moving the erect penis inside the vagina.

#### Plan for the Future (Session 8)

In the last session, participants will be asked to reassess their training goals and to identify their personal warning signs for GPPPD setbacks. Additionally, they will be given the opportunity to write a letter to themselves describing their life after 4 more weeks of exercises, which they can refer to in the future if they wish.

#### Booster Session

Four weeks after completing the intervention, participants will be given the option of completing a booster session and evaluating their training progress. They will revisit the letter they wrote to themselves in the last session, reassess their goals, and make plans concerning insertion exercises or sexual activities.

### Support

Participants are supported by a personal eCoach. The focus of the coaching is to reinforce treatment efforts, answer questions, and to motivate participants. The eCoaches are female psychologists or trained and supervised psychology students, and will follow guidelines outlining the feedback process as defined in the standardized manual for the intervention. The eCoaches will send reminders in cases in which the participants do not complete one session within 7 days. After each session, participants will receive personalized written feedback on the exercises they have completed from the eCoach within 48 hours. The eCoach also closely monitors and reacts to potential signs of deterioration or other potentially adverse events. Guidelines for feedback follow principles that have been employed in a large number of previous studies from our research group (56, 72).

### Primary and Secondary Outcomes

Primary outcome will be sexual intercourse at posttreatment. In secondary analyses, the effects of the intervention, e.g., on nonintercourse penetration behavior, fear of sexuality, sexual functioning, and cognitions regarding vaginal penetration, will be examined.

### Outcome Measures

#### Intercourse Penetration

The seven-item PEQ will be used as a primary outcome measure. Successful intercourse penetration (SIP) will be measured by one item assessing the degree to which the insertion of the partner’s penis was possible. The items will be answered on a 4-point Likert scale (0 = not attempted; 1 = attempted, but unsuccessful; 2 = attempted and sometimes successful; 3 = attempted and always successful). Previous cases of women reaching SIP prior to treatment completion have shown that they are susceptible to study dropout (67). For that reason, participants who do not fill out the PEQ online, (1) are scheduled for a telephone assessment or (2) can report to their eCoach whether intercourse penetration was successful.

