## Methods

### Design

An RCT will be conducted to compare the IG (Paivina-Care) with a WCG. Self-reported assessments will take place at baseline (T1), peritreatment (after completion of Session 5, T2 in IG), posttreatment (after completion of Session 8 or 12 weeks after randomization, T3) and at a 6-month follow-up (T4; see Figure 1 for a detailed overview). Self-reported data will be collected using a secure online-based assessment system (AES, 256-bit encrypted). All procedures involved in the study will be consistent with the generally accepted standards of ethical practice. The study was approved by the Friedrich-Alexander University Erlangen-Nürnberg ethics committee (no. 324_15B). The trial is registered in the German clinical trials register under DRKS00010228. All participants gave written informed consent in accordance with the Declaration of Helsinki.

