#### Stepwise Procedure: Assessment of Eligibility and Randomization

Women who sign up as potential participants will receive an online information letter with detailed information on the study procedures. They will be asked to provide an email address that they want to use for the study and a first and last name (which can be pseudonyms if desired). The women will be informed that they can withdraw from the intervention and/or study at any time without any negative consequences. Applicants who intend to participate in the study will be asked to complete online screening questionnaires that assess inclusion and exclusion criteria. If responses to this questionnaire indicate that participants might be affected by one of the mental health disorders listed as exclusion criteria above, participants will be scheduled for the SCID-I *via* telephone. Women who meet all of the inclusion criteria and none of the exclusion criteria and who complete the baseline assessment and return the informed consent form will be considered for the study and randomly allocated to one of the two study conditions. Randomization will take place at an individual level. This process will be completed by an independent researcher not otherwise involved in the study using an automated computer-based random integer generator (randlist). Until this process has been completed, the results will not be known by participants, researchers involved in recruitment or eCoaches. Participants will be informed of the outcome of the randomization, and participants in the IG will receive immediate access to the program. Participants in the WCG will receive access to the program 6 months after study intake.

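### At T3 the eCoach fallback for a missing primary outcome is in effect open only to the intervention group, so ascertainment may differ by arm and by outcome and may favour the intervention

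*Protocol article*

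**What the plan says.** The section Intercourse Penetration makes one PEQ item, scored 0 to 3, the measure of successful intercourse penetration. Women who do not complete it online are either scheduled for a telephone call or have a second route, worded "2) can report to their eCoach whether intercourse penetration was successful". No arm is named. The reason given is this: "Previous cases of women reaching SIP prior to treatment completion have shown that they are susceptible to study dropout".

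Three other sections determine who can use the second route:

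- Support: "Participants are supported by a personal eCoach", and "The focus of the coaching is to reinforce treatment efforts, answer questions, and to motivate participants".
- Stepwise Procedure: after randomization "participants in the IG will receive immediate access to the program", whereas "Participants in the WCG will receive access to the program 6 months after study intake".
- Design: the primary time point is "posttreatment (after completion of Session 8 or 12 weeks after randomization, T3".

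Statistical Analyses plans a chi-square test for the primary outcome, analysis by intention to treat, multiple imputation for missing values, and additional completer analyses.

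**The concern.** Read together, these sections give the two arms different ways of supplying the sole primary endpoint. A waitlist woman who skips the questionnaire can be recovered only by telephone. An IG woman can be recovered by telephone or by telling the person who is coaching her. Because the two routes are joined by an or, a coach report may also replace the call.

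The extra route is optional, and its purpose is to catch women who succeeded and stopped responding, so successes are likelier than failures to come in through it. The recipient delivers the treatment and is not a blinded assessor.

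Neither intention to treat nor multiple imputation repairs this. Both take the recovered outcomes as observed data, and an imputation model that includes arm carries the enriched IG rate into the values it fills in. At stake are the estimated difference and the type I error of the primary test.

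**Working it through.** **1. The plan's own figure.** Inputs from Sample Size Calculation: w = 0.20, 80% power, two-sided alpha 0.05. N = (1.960 + 0.842)² / 0.20² = 7.849 / 0.04 = 196.2, so 197. The stated 200 reproduces, and this point does not affect it. Allocation is not stated; 1:1 (100 per arm) is assumed. As a yardstick, w = |p1 − p2| / (2√(p̄(1 − p̄))). For 20% against 38.2%, p̄ = 0.291 and w = 0.182 / (2 × 0.454) = 0.20, so the detectable difference is about 18 points.

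**2. Who has the route.** A waitlist woman cannot complete Session 8 before she has access, so her T3 falls at 12 weeks. Access and coaching come at 6 months. Route 2 is therefore unavailable to her at T3. This is inferred from the sections together; no sentence states it.

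**3. Formula.** The article gives no success rate, non-response rate or telephone reach, so all of the following are assumed:

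- p: true success rate, equal in both arms (no effect)
- m: share not completing the PEQ, equal in both arms and unrelated to outcome
- f: share of those reached by telephone, equal in both arms
- r = m(1 − f): share still missing after the telephone calls
- s, u: probability that a still-missing IG woman tells the eCoach of a success (s) or of a failure (u)

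Observed IG rate = p(1 − r + rs) / [p(1 − r + rs) + (1 − p)(1 − r + ru)]. The observed waitlist rate is p. With s = 1 and u = 0 the IG rate becomes p / [1 − r(1 − p)]. Example: p = 0.20, m = 0.40, f = 0 gives 0.20 / 0.68 = 29.4%, a spurious +9.4 points.

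Type I error comes from simulation: 200,000 trials per scenario, 100 per arm, Pearson chi-square. Complete cases by arm stand in for imputation with arm in the model.

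Results for p = 20%, s = 1, u = 0:

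| Telephone reach | Bias in points at m = 10 / 20 / 30 / 40% | Type I error |
|---|---|---|
| 0% | +1.7 / +3.8 / +6.3 / +9.4 | 6.0 / 9.0 / 14.5 / 23.1% |
| 50% | +0.8 / +1.7 / +2.7 / +3.8 | 5.2 / 5.9 / 7.1 / 9.0% |
| 80% | +0.3 / +0.7 / +1.0 / +1.4 | 5.1 to 5.6% |

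**4. Other assumed values, with no telephone reach and m from 10 to 40%.**

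- p = 10%, s = 1, u = 0: +1.0 to +5.6 points, type I error 5.5 to 15.0%.
- p = 30%, s = 1, u = 0: +2.3 to +11.6 points, type I error 6.3 to 28.5%.
- p = 20%, half of missing successes reported (s = 0.5, u = 0): +0.9 to +5.0 points, type I error 5.3 to 10.1%.
- Successes and failures equally likely to be reported (s = u): the formula returns p exactly, and type I error is 5.0%.

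**5. Dropout related to success.** Let 40% of IG successes, 20% of IG failures and 20% of the waitlist group be missing, with p = 20% and no telephone reach.

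- No coach route: 0.12 / (0.12 + 0.64) = 15.8%, or −4.2 points.
- Half of missing successes reported: 0.16 / (0.16 + 0.64) = 20.0%, or 0.0 points.
- All reported, no failures: 0.20 / (0.20 + 0.64) = 23.8%, or +3.8 points.

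With 50% of IG successes missing, the three values are −6.5, −1.0 and +3.8.

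**The case against.** A reader might infer that the primary comparison is biased toward the intervention, with a type I error of 10% or more. The article does not support that, for three reasons.

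First, the telephone assessment names no arm and is worded as something that is scheduled, while the coach report is only permitted. The large figures need a telephone follow-up that reaches almost nobody. At 80% reach the bias is 1.4 points or less.

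Second, the text allows a woman to report the result either way, so failures can come in too. That reports will be mostly successes is plausible from the stated reason, but it is not documented.

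Third, the same stated reason implies that missing IG women may be disproportionately successes. The coach route may then correct a bias against the intervention, as step 5 shows.

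All three stand, and they remove any claim of a certain direction or a large size. It is also fair that a time window, the order of the routes and the coding of coach reports may sit in documents not shown; this point does not rest on their absence. The imputation model may use more than arm, for instance the PEQ at T2 in the IG, so step 3 is an approximation.

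What survives is the structure: the balance in step 5 depends on a voluntary reporting rate that nobody controls and that exists in one arm only. The additional completer analysis restricted to women who filled out the questionnaires does not settle it, because it may simply drop the recovered women.

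**Conclusion.** The point holds as a risk of differential, outcome-dependent ascertainment of the primary endpoint that may favour the intervention. It is not a demonstrated bias. That the route is open only to the IG at T3 is a firm inference from the sections cited.

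Under no true effect, a 20% success rate, 10–40% non-response unrelated to outcome, and full reporting of successes but not failures, the spurious difference runs from +0.3 points at 80% telephone reach to +9.4 points at none, against a detectable difference of about 18 points. Type I error runs from about 5.1% to 23%. None of these rates is in the article. If IG successes drop out more often, the net effect can be zero or, with little or no rescue, against the intervention. The rule is worth changing because a symmetric alternative is already planned.

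**What to change.** For every woman in either arm who does not complete the PEQ at T3, obtain the intercourse item (item 7) through the telephone assessment already planned, with the same wording, 4-point response and window. An assessor outside the coaching is preferable. Use a report to the eCoach only to trigger that call. Record the source of each primary outcome (online, telephone, coach only). Keep coach-only reports out of the primary dataset, and show the result with them included as a sensitivity analysis.

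The cost is a wording change in the outcome section and the eCoach manual; telephone assessment is already part of the plan. The downside is that some IG outcomes known only through the coach become missing in the primary analysis. Where telephone contact fails and IG successes drop out more often, this could understate the IG success rate. The sensitivity analysis shows by how much, and persistent calling in both arms limits it.

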#### Nonintercourse Penetration

Successful nonintercourse penetration will be measured by the remaining six items of the seven-item PEQ. These items assess the degree to which insertion of one or two fingers or another object such as a tampon or a dilator by the woman or her partner was possible. Participants will be asked to answer questions referring to the past two weeks. Cronbach alpha was found to be good (α = 0.81) for this scale (67).

#### Fear of Sexuality

The frequency of a woman’s fear experienced in different sexual situations will be measured using the Fear of Sexuality Questionnaire (FSQ) (73). The FSQ consists of the five-item subscale fear of noncoital sexual activity and the three-item subscale fear of coitus. The items are answered on a 5-point Likert scale ranging from 1 = never to 5 = always. The internal consistency of this measure has been found to be good with a Cronbach alpha of α = 0.82–0.84 for fear of noncoital sexual activity and α = 0.82–0.86 for fear of coitus in samples of women with vaginismus (67, 73).

#### Cognitions Regarding Vaginal Penetration

Vaginal penetration cognitions will be assessed with the Vaginal Penetration Cognition Questionnaire (VPCQ) (74), which is comprised of the five subscales: control, catastrophic and pain, self-image, positive, and genital incompatibility cognition. This self-report instrument uses a 7-point Likert scale anchored by 0 = not at all applicable and 6 = very strongly applicable. Reliability of these five VPCQ subscales ranges from α = 0.70 to α = 0.83 in a sample of women with vaginismus and dyspareunia.

#### Sexual Functioning

To measure different domains of female sexual functioning, the Female Sexual Function Index will be used (75–77). This self-report instrument consists of the following 6 subscales: sexual desire, sexual arousal, lubrication, orgasm, pain and sexual satisfaction. The questionnaire uses a 6-point Likert scale anchored by 0 = no sexual activity and 5. The measure allows for the calculation of specific indexes for each dimension and of an overall sexual function index. The internal consistency ranges from α = 0.82 to α = 0.93 in women with female sexual arousal disorder (76) and from α = 0.76 to α = 0.93 in a sample of women with vaginal penetration difficulties (67).

#### Satisfaction with the Intervention

Patient satisfaction with the intervention will be measured by using an adaptation of the Client Satisfaction Questionnaire (CSQ-8, German: ZUF-8) optimized for the assessment of client satisfaction with Internet interventions (CSWIQ-8) (78, 79). The CSQ-8 is a validated eight-item instrument with high internal consistency (α = 0.93) (79). The adapted version, validated for the assessment of client satisfaction in Internet-based interventions, has repeatedly proven to have high internal consistency (α = 0.92–0.94) (56, 80, 81) and is associated with treatment adherence and outcome (80).

#### Other Measures

Other measurements include the Structured Clinical Interview for DSM-IV Axis I Disorders (SCID-I), socio-demographic variables (e.g., age, gender, duration of symptoms, etc.), the Well-Being Index (WHO-5) (82–84), the Self-Esteem Scale (85, 86), and the Health Action Process Approach Questionnaire (87) adapted to treatment adherence. Experiences of sexual abuse will be measured with the sexual abuse subscale of the Childhood Trauma Questionnaire (88, 89) and an item adapted to experiences following the age of 18. To assess relationship quality, we will use the Dyadic Coping Inventory (90, 91) and the Partnership Questionnaire Short Form (92). The State Trait Anxiety Inventory (93, 94) and the Generalized Anxiety Disorder 7-item Scale (GAD-7) (95, 96) will be used to assess general anxiety sensibility. Potential negative effects of the Internet-based intervention will be assessed using the Inventory for the Assessment of Negative Effects in Psychotherapy (97). We will also measure potential dropout reasons and the utilization of additional help with self-developed items. Participants will need approximately 40 min to complete all questionnaires at baseline and 30 min at follow-ups. For an overview of all outcome measures, see Table 2.

**Table 2 T2:** Measures.

	T0	T1	T2	T3	T4
Primary Endpoint Questionnaire	✓	✓	✓	✓	✓
Fear of Sexuality Questionnaire	–	✓	✓	✓	✓
Vaginal Penetration Cognition Questionnaire	–	✓	✓	✓	✓
Female Sexual Function Scale	–	✓	–	✓	✓
**Other measurements**					
Socio-Demographic Questionnaire	✓	–	–	–	–
Childhood Trauma Questionnaire	–	✓	–	–	–
Dyadic Coping Inventory	–	✓	–	✓	✓
Partnership Questionnaire Short Form	–	✓	–	✓	✓
State Trait Anxiety Inventory	–	✓	–	✓	✓
Generalized Anxiety Disorder 7-Item Scale	–	✓	–	✓	✓
Well-Being Index	–	✓	–	✓	✓
Self-Esteem Scale	–	✓	–	–	–
Health Action Process Approach Questionnaire	–	✓	✓	–	–
Client Satisfaction Questionnaire	–	–	–	✓	–
Inventory for the Assessment of Negative Effects in Psychotherapy	–	–	–	✓	✓
Regular practicing of the exercises	–	–	–	✓	✓
Potential dropout reasons	–	–	–	✓	✓
Utilization of additional help	–	–	–	✓	✓
